## Discussion

Although preventive tasks should be a central part of the work of OPs in the Netherlands, implementation of preventive tasks is insufficient. To improve the uptake of preventive tasks by OPs, insight is needed into the barriers and facilitators for the utilization of preventive tasks, and into strategies how to overcome these barriers. Making use of literature and stakeholder opinion, and following the Implementation Mapping protocol, we developed an intervention to stimulate OPs to implement preventive tasks in their current practices. The evaluation phase will include an effect evaluation and process evaluation. The aim of this evaluation phase is to examine if this intervention is successful in supporting OPs to implement preventive activities, specifically aimed to prevent work-related mental health problems.

### Relevance and expected impact

More knowledge and awareness of the value of prevention among OPs can ultimately also lead to more knowledge and awareness among employers and employees about work-related mental health problems and preventive measures. It is therefore anticipated that better implementation of preventive tasks by OPs will lead to reduced numbers of work-related mental health problems and to both organizational and individual gains. For OPs, better execution of preventive tasks might not only make the work more varied and attractive, but may also lead to more job satisfaction. For employees, more prevention might contribute to increased awareness, increased job satisfaction and improved workplace culture [27]. Since negative job attitudes and high job demands are found to be predictors of burn-out, increased job satisfaction and improved workplace culture are expected to ultimately result in lower number of burn-out related complaints and reduced health care and sick leave costs [28]. For the organization or employer benefits are, among others, increased work productivity, reduced absenteeism or presenteeism, improved workplace culture and company image [27]. Since episodes of sick-leave due to stress complaints have a long duration and high associated costs (101 working days and 19,151 euros), preventing sick leave can avoid high costs for the employer [4].

If the intervention described in this paper has proven to be effective in supporting OPs in their preventive tasks, widespread implementation of the intervention is anticipated. For this, an additional implementation and dissemination plan will be developed. Moreover, the form of the intervention (peer group supervision focused on goal setting) may also be applicable to prevention of other work-related health problems or relevant themes other than prevention. The process evaluation can help to understand if and how the intervention can be improved in order to do so.

### Methodological considerations

The chosen study design of a cluster randomized controlled trial is a suitable design since the intervention will be delivered at group level [16]. However, one limitation of this design is that participants within a cluster are more likely to resemble each other, and their results can therefore not be seen as independent [23]. In addition, cluster-RCTs have a higher risk of selection and dilution bias than individual RCTs [29]. These methodological limitations have been accounted for in this study by identifying the participants and obtaining their informed consent prior to cluster allocation [29]. This is possible, because existing peer support groups are recruited in this study. A limitation of the designed intervention is that it cannot tackle all identified barriers for the execution of preventive tasks. Some barriers are contextual factors, and related to the organization and financing of the occupational health care system in the Netherlands. These contextual barriers are not easy to solve within the current legislation and regulations. This study is thus conducted within the context of the current system.

Besides these limitations, this study also has some advantages. So far, most research has been limited to only the identification of barriers and facilitators to the implementation of preventive tasks by the OP. Research into the development and evaluation of strategies or interventions that tackle these factors is lacking. Moreover, most studies on the role of the OP focus on absence and reintegration guidance, and not on stimulating the preventive role of OPs. This study fills this research gap. An advantage of using the IM protocol is that we systematically work towards the development of an intervention to support OPs in the execution of their preventive tasks. Another strength is the use of both knowledge from research and literature, as well as practical knowledge from the stakeholders involved. In addition, the strategies used in the intervention are evidence-based and translated to the Dutch context and context of this research. In doing so, we adhere to the existing structure and method of peer support groups. This way, our implementation protocol is not only scientifically relevant, but also fits to practice. The evaluation of this study will focus on the effectiveness and process. This makes our evaluation more comprehensive and will allow us to learn from the implementation process to eventually improve the intervention, before implementing on a wider scale.

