#### Sample size and power calculation

The sample size for this study was based on estimating an effect on the primary outcome, the self-reported percentage of time spent on preventive tasks. Using a one-sided Pearson’s chi-squared test of proportions at alpha = 0.05, assuming 0.1 and 0.25 of the total percentage of working hours per week being assigned to prevention tasks in the control and in the treatment groups, respectively, 80 participants were needed in each group to achieve a statistical power of 0.8. Considering a loss to follow-up of 20%, this study would require a sample size of 200 individual participants, of which half in the control and half in the intervention condition. Taking into account that each peer group consists of approximately eight people, this corresponds to approximately 25 peer groups. This analysis was done using the procedure power in SAS, version 9.4, and in consultation with an experienced statistician.

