#### Randomization, treatment allocation and blinding

After each individual OP has given their written informed consent for participating in the evaluation and has filled in the baseline questionnaire (T0), randomization will take place at the level of the existing peer groups. Participating groups of OPs will be randomly assigned to (1) the peer group supervision plan directed to the implementation of preventive tasks targeting work-related mental health problems (intervention groups) or (2) the usual peer group supervision condition (control groups). The control groups will be put on a waiting list and receive the peer group supervision materials after the 12 months follow-up of this study. To avoid bias, the randomization process will be executed by two independent researchers. Researcher 1 will assign consecutive numbers to each participating peer group. A computer-generated randomization will then be performed by researcher 2, in order to assign each number to either the intervention or control group. This way, allocation to either one of the groups cannot be influenced. Because of the intervention, blinding for allocation on the level of the participant (OP) is not possible.

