##### Data analysis

Data at baseline, 6 months (T1) and 12 months follow-up (T2) will be presented using descriptive statistics. To investigate the effectiveness of the intervention, differences between the intervention and control group in the outcomes at baseline, T1 and T2 will be analysed making use of longitudinal linear or logistic mixed models. If necessary, baseline differences between the intervention and control group will be adjusted for. Consistent with the design of the cluster-RCT and to avoid bias, analyses will be performed following the intention-to-treat principle. This means that all participants randomized will be kept in the groups they were randomized to, regardless of the intervention they received in practice [23]. For the analyses a two-tailed significance level of < 0.05 will be considered statistically significant. All statistical analyses will be performed with SPSS software, version 28.0.1.1.

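### The protocol article credits consent before allocation with dealing with within-group correlation, which it cannot do, and states no other method that handles peer-group clustering

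*Protocol article*

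**What the plan says.** All places are in the protocol article.

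- **Randomization, treatment allocation and blinding:** "randomization will take place at the level of the existing peer groups".
- **Methodological considerations**, first limitation: "participants within a cluster are more likely to resemble each other, and their results can therefore not be seen as independent". Second limitation: "cluster-RCTs have a higher risk of selection and dilution bias than individual RCTs". The next sentence gives one remedy: "These methodological limitations have been accounted for in this study by identifying the participants and obtaining their informed consent prior to cluster allocation".
- **Data analysis:** differences between the arms at baseline, T1 and T2 "will be analysed making use of longitudinal linear or logistic mixed models". No random effect is named at any level. The one mention of the cluster design leads elsewhere: "Consistent with the design of the cluster-RCT and to avoid bias, analyses will be performed following the intention-to-treat principle". On the test: "For the analyses a two-tailed significance level of < 0.05 will be considered statistically significant".
- **Sample size and power calculation:** a one-sided "chi-squared test of proportions at alpha = 0.05" comparing 0.10 with 0.25 gives 80 per arm. This is raised to 200 in total for 20% loss, or about 25 groups of about eight. Group size serves only to turn participants into groups.

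**The concern.** The two limitations need different remedies. Recruitment bias depends on whether people join knowing their arm, so obtaining consent first is a sensible safeguard. Correlation within a group comes from shared habits, setting and discussion, and it is the same whenever consent is signed. It has to be handled in the analysis model and in the sample size.

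On its plain reading, the article claims a property that the design does not have. Someone who trusts the sentence could conclude that nothing more is needed and fit a model with repeated measures within OP only. OPs in one peer group would then be treated as independent although the arm is assigned to about 25 groups. Standard errors would be too small, confidence intervals too narrow, and false positives on the primary outcome too frequent.

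Correlation that develops after baseline is plausible here. Step 4 describes goals set with colleagues' input, shared best practices and a trained chair for each intervention group.

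**Working it through.** **1. The plan's own figure.** Inputs from Sample size and power calculation: p1 = 0.10, p2 = 0.25, one-sided alpha 0.05, power 0.80. Use the pooled-variance formula without continuity correction, with mean proportion 0.175:

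n = [1.645 × √(2 × 0.175 × 0.825) + 0.842 × √(0.10 × 0.90 + 0.25 × 0.75)]² / 0.15² = (0.884 + 0.443)² / 0.0225 ≈ 78.3, so 79 per arm.

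The article states 80, at which power is 0.808. Then 80 / 0.8 = 100 per arm, 200 in total, and 200 / 8 = 25 groups. The figure reproduces as an individually randomised calculation, so no allowance for clustering is hidden in it.

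**2. Error if peer group is left out of the model.** With m OPs per group, the design effect is DE = 1 + (m − 1) × ICC. The actual error of a nominal two-sided 5% test is 2 × [1 − Φ(1.96 / √DE)]. Group size is m = 8 as stated, or 8 × 0.8 = 6.4 after the planned loss. The ICC range is an assumption.

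| Assumed ICC | DE, m = 6.4 | Error | DE, m = 8 | Error |
|---|---|---|---|---|
| 0.01 | 1.054 | 5.6% | 1.07 | 5.8% |
| 0.02 | 1.108 | 6.3% | 1.14 | 6.6% |
| 0.05 | 1.27 | 8.2% | 1.35 | 9.2% |
| 0.10 | 1.54 | 11.4% | 1.70 | 13.3% |

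Example: for ICC 0.05 and m = 8, √1.35 = 1.162, 1.96 / 1.162 = 1.687, and 2 × [1 − Φ(1.687)] = 0.092.

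A simulation under no effect (12 versus 13 groups of 8, 20% loss, 6,000 runs each) agrees with the m = 6.4 column: 5.7%, 8.7% and 11.5% for ICC 0.01, 0.05 and 0.10. A t test on group means gave 4.9%, 5.1% and 5.0%.

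**3. What the baseline measurement changes.** The formula describes a comparison at follow-up. The plan also measures T0, so a second simulation used 25 groups of 8 with baseline and two follow-ups averaged (5,000 runs each). Single-measurement variance at follow-up was about 1, with 0.5 between OPs.

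| Group variance | Follow-up, group ignored | Change from baseline, group ignored | Follow-up group means |
|---|---|---|---|
| None | 5.3% | 5.4% | 5.3% |
| 0.05, constant over time | 10.0% | 5.0% | 4.7% |
| 0.10, constant over time | 15.9% | 4.3% | 5.2% |
| 0.025 constant + 0.025 after baseline | 10.6% | 7.8% | 5.2% |
| 0.05, arising after baseline | 10.8% | 11.4% | 5.2% |
| 0.10, arising after baseline | 15.4% | 16.9% | 5.5% |

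The follow-up column lies above the formula because averaging two measurements reduces residual variance and so raises the ICC. For group variance 0.05 it is 0.05 / (0.05 + 0.50 + 0.225) = 0.065.

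A constant group effect cancels out of the change from baseline, and the excess goes. An effect that arises after baseline does not cancel.

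**The case against.** **The sentence may mean only selection and dilution bias.** It directly follows the statement about those biases and shares its citation, while non-independence carries a different one. That reading is possible. But the sentence refers back to the limitations in general after both have been listed, and non-independence is the first of them. Under the narrower reading the article still gives no remedy for non-independence.

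**The analysis text does not leave peer group out.** This stands. A reader might infer that clustering is not handled and that the error rate exceeds 5%. The article does not support that. Data analysis lists no random effects at all, neither OP nor peer group, and the word longitudinal describes the data rather than the full random structure. The authors plainly know that members of a group are not independent. The structure may be set out in a full protocol or statistical analysis plan that is not shown, and its absence from an article is no fault in itself. Nor does the article commit to a large-sample z test.

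**The size is conditional.** This stands too. It needs peer group omitted, a positive ICC, and a group effect that does not cancel against baseline. OPs may also decline the evaluation or be excluded (Study population and recruitment), so the number analysed per group, and with it the design effect, may be smaller.

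What survives is the misattributed remedy, which a specification elsewhere would not make correct.

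**Conclusion.** The concern holds in a limited form. On its plain reading, Methodological considerations credits consent timing with dealing with within-group correlation, which it cannot do. No section states a method that does: Data analysis ties the cluster design only to intention-to-treat, and the sample size contains no design effect.

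Whether the primary test is affected depends on the model actually fitted. With repeated measures within OP only, the two-sided error would be about 5.6% to 11.4% at 6.4 OPs per group, or 5.8% to 13.3% at 8 per group, for an assumed ICC of 0.01 to 0.10. These are approximations for a comparison at follow-up. The excess largely vanishes for a change-from-baseline contrast if the group effect is constant over time, and it persists if the effect arises after baseline. If peer group is already properly represented in the model, only the wording needs correction.

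The one-sided planning test set against the two-tailed analysis is a separate matter.

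**What to change.** 1. **Methodological considerations:** limit the sentence to selection bias. Say that consent before allocation reduces selective recruitment, and that non-independence within peer groups is handled in the analysis model.
2. **Data analysis:** state that the mixed models include random intercepts for peer group and for OP within peer group. For the linear models, preferably use small-sample degrees of freedom (Satterthwaite or Kenward-Roger). With about 25 groups in two arms the reference t has about 23 degrees of freedom, and the critical value is 2.07 rather than 1.96.
3. **Role of T0:** say how baseline enters. If T0 is modelled as an outcome, a peer-group intercept that is constant over time cancels from the change contrast and cannot absorb a group effect arising later. Either add a peer-group-by-time random term, or use T0 as a covariate with T1 and T2 as outcomes.

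The cost is two sentences, one or two extra model terms, and somewhat wider confidence intervals. No change to data collection is needed.

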## Data Availability

Data sharing is not applicable to this article as no datasets were generated or analyzed during the current study.

## Abbreviations

ASE: Attitude, social influence and self-efficacy
IM: Implementation Mapping
IM-PROmPt-study: Implementation of PReventive tasks by Occupational Physicians Study
MIDI: Measurement Instrument for Determinants of Innovation
OHS: Occupational health and safety services
OP(s): Occupational physician(s)
QQEW: Questionnaire on the Experience and Evaluation of Work
SME: Small and Medium Enterprises
RCT: Randomized Controlled Trial
